# Thiamine versus placebo in older heart failure patients: study protocol for a randomized controlled crossover feasibility trial (THIAMINE-HF)

**DOI:** 10.1186/s40814-018-0342-0

**Published:** 2018-09-20

**Keywords:** Heart failure, Thiamine, Placebo, Crossover, Randomized controlled trial, Elderly

## Abstract

**Background:**

Heart failure (HF) is a major cardiovascular disease with increasing prevalence. Thiamine deficiency occurs in 33% of patients with HF. However, the effectiveness of thiamine supplementation in HF is not known.

**Methods:**

In a placebo-controlled randomized two-period crossover feasibility trial, patients age ≥ 60 years with HF and reduced ejection fraction (HFrEF, EF ≤ 45%) will be randomized to thiamine 500 mg oral capsule once daily or placebo for 3 months, then crossed over to the other intervention after a 6-week washout period. The primary outcome is recruitment rate. Secondary outcomes include feasibility and clinical measures. Feasibility outcomes include refusal rate, retention rate, and compliance rate. Secondary clinical outcomes include left ventricular ejection fraction, peak global longitudinal strain measured by echocardiography, N-terminal prohormone of brain natriuretic peptide (NT-proBNP), New York Heart Association (NYHA) functional class, Kansas City Cardiomyopathy Questionnaire (KCCQ) quality of life score, and clinical outcomes (all-cause mortality, HF hospitalizations, and HF emergency room visits).

**Discussion:**

Thiamine is potentially a safe and low-cost treatment for older patients with HFrEF. Results from this study will inform the feasibility of a large clinical trial with clinical endpoints. The findings will be published in a peer review journal and presented at a relevant conference. This study has received full approval from the Hamilton Integrated Research Ethics Board (18-4537) and Health Canada (210603). This trial is funded by the Hamilton Health Sciences New Investigator Grant (15-387) and the McMaster/St. Peter’s Hospital Chair of Aging.

**Trial registration:**

NCT03228030 (ClinicalTrials.gov), registered July 24, 2017.

## Background

Approximately 500,000 Canadians are living with heart failure (HF), with a prevalence of 1–2% [1]. Despite optimal therapy, HF patients experience adverse events, such as hospital admissions and mortality. The 1-year mortality for a hospitalized patient with HF is 33% in Canada [2] and readmission rates are nearly 50% within 1 year of hospitalization, increasing with age [3]. The total health expenditure related to HF is estimated at $3.9 billion per year in Canada [4].

A new direction in HF research emphasizes the role of decreased energy production as a mechanism [5]. Thiamine, also known as vitamin B1, is an essential micronutrient that is required for energy production in the heart [6]. This vitamin is not synthesized in the body, and total body store only amounts to 25–30 mg, which is mostly contained in the skeletal muscles, heart, brain, and kidneys [7]. Thiamine is ingested and absorbed in the jejunum and ileum by active transport. Once absorbed, free thiamine enters the organs, central nervous system, and erythrocytes. Within these tissues and cells, free thiamine is phosphorylated to thiamine pyrophosphate (TPP), which is the biologically active form. Thiamine status is quantified by measuring erythrocyte TPP using high-performance liquid chromatography (HPLC) [8].

Thiamine deficiency is common in patients with HF, with a recent study demonstrating a prevalence of 33% [9]. Thiamine plays an important role in cellular energy production, and its deficiency gives rise to both cardiovascular and neurological consequences. The clinical syndrome of wet beriberi, which is the result of severe thiamine deficiency, resembles HF, with tachycardia, hypotension, and peripheral edema as presenting findings [10]. Heart failure with reduced ejection fraction (HFrEF) is associated with thiamine deficiency in those not taking supplements (49% vs. 24%, *p* = 0.03) [9]. The use of diuretics is also a risk factor for thiamine deficiency, as demonstrated in older studies [11–15]. Age also appears to be an important risk factor, with the prevalence of thiamine deficiency increasing with age [16]. One study of thiamine deficiency in younger patients with HF (*n* = 38; mean age = 47) found only one deficiency case [17].

We propose a randomized placebo-controlled two-period crossover feasibility study of thiamine supplementation in HF. This randomized controlled trial (RCT) is warranted because (i) thiamine deficiency is common in this population and appears related to reduced left ventricular ejection fraction (LVEF); causality is uncertain, so an RCT is necessary to ascertain whether the relationship is causal; and (ii) thiamine supplements have a wide therapeutic window, making this intervention safe and widely applicable. The aims of the present feasibility study are (i) to determine the feasibility of recruitment for an RCT of thiamine supplementation, (ii) to provide data that will permit refinement of sample size estimates for an RCT that is powered for clinical endpoints, and (iii) to optimize trial procedures with a view to conduct a definitive, larger trial.

## Methods

### Design and setting

This is a randomized placebo-controlled two-period crossover feasibility study of thiamine supplementation in HF. The study will include symptomatic, stable older patients with decreased LVEF and recent HF hospitalization in the past 12 months. The chosen population includes patients who are likely to have thiamine deficiency (older HF patients with decreased LVEF) and likely to respond to therapy. Including patients with a recent hospitalization will increase the chances of clinical events, such as recurrent hospitalization or death [18, 19]. A two-period crossover design reduces variance between the treatment and control arms. We will test the feasibility of recruitment at St. Joseph’s Hospital (SJH), and two sites of the Hamilton Health Sciences Corporation (Juravinski Hospital and Hamilton General Hospital) in Ontario, Canada. Eligible patients will be identified on inpatient and outpatient medical units at these sites. Subsequent visits will occur at the Hamilton General Hospital.

### Inclusion criteria

Age ≥ 60 years.New York Heart Association (NYHA) class II–IV symptoms.Recent HF-related admission in the past 12 months (defined as HF being reason for admission or HF being a complication during a hospital admission).LVEF ≤ 45% on 2D/3D echocardiography or radionuclide angiography (RNA) in the past 12 months (on optimal therapy).Medically optimized prior to enrolment with angiotensin-converting enzyme inhibitor or angiotensin receptor blocker (± neprilysin inhibitor), β-blocker, and/or aldosterone antagonist at target or maximally tolerated doses.Stable on medications without hospitalization in the past month.

### Exclusion criteria

Taking > 2.5 mg/day of thiamine supplement.Unable to swallow study medication.Clinical indication for thiamine supplementation including symptomatic thiamine deficiency (Wernicke’s encephalopathy, severe malnutrition, refeeding syndrome) and heavy alcohol use defined as > 15 standard drinks per week in men and > 10 standard drinks per week in women [20].End-stage renal disease on dialysis.Severe mitral valve disease because this impacts the accuracy of speckle tracking analysis on echocardiography [21].Non-English speaking (unable to complete questionnaires).Unable to provide written consent.Cognitive impairment without a caregiver administering medications.Expected survival < 1 year due to non-cardiac disease.Expected heart transplantation in < 6 months (± left ventricular assistive device).Allergies to the ingredients of the study medication or placebo.

### Screening

Eligible patients will be screened by a research nurse in the Heart Function Clinic at Hamilton General Hospital and by physician investigators on medical inpatient and outpatient units at St. Joseph’s Healthcare Hamilton and sites of Hamilton Health Sciences. Informed consent will be obtained. Older patients with HF often have concomitant cognitive impairment [22]. If a diagnosis of cognitive impairment or dementia is documented or known by the patient/informal caregiver (spouse, family member, or friend involved in patient’s health care), then a caregiver must be available to provide medications daily. If there is any doubt about a participant’s ability to adhere to study medications or protocols, the study nurse will inform the supervising principal investigator, who will make an assessment. Cognitive impairment on its own is not an exclusion criteria as long as there is a reliable way of administering medications (e.g., supervision). However, all participants, even those with cognitive impairment, will be required to provide written informed consent independent of the informal caregiver. If the participant, due to cognitive impairment, cannot comprehend sufficiently to provide informed consent, he or she will be excluded from participation.

### Randomization, enrolment, and crossover arrangement

Identical bottles containing either placebo or thiamine will be labeled by the hospital pharmacy using a computer-generated randomization list (allocation concealment). Only the pharmacy and our statistician (LM) have access to the randomization list. All participants, investigators, and the research nurse will be blinded to group assignments.

Consented patients will be randomized to thiamine or placebo, taken orally once daily for 90 days during the first period. The study medication is *thiamine mononitrate*. Capsules in 500 mg dose are produced by the Accurex Health Care Manufacturing Inc. along with identical placebo capsules containing inert filler. Participants will be instructed not to take the following foods or health products within 2 h of taking the study medication: areca (betel), horsetail (equisetum), raw freshwater fish, and raw shellfish. These foods interfere with thiamine absorption.

Patients will be sequentially assigned to the two groups in a typical AB/BA crossover design [23]. The first group (AB) will be given thiamine (treatment A) for 90 days, followed by a 6-week washout period during which no supplements are given. The patients will then be given placebo (treatment B) for 90 days. The second group (BA) will start with placebo, followed by thiamine. Compliance will be tracked by pill counts and thiamine blood test at each clinic visit (0, 3, 4.5, and 7.5 months). Patients may continue with concomitant medical care.

### Washout period

The rationale for a 6-week washout period is based on previous studies; the half-life of thiamine is 9–18 days based on a physiology study in young healthy men with radiotagged thiamine [24]. Assuming 4–5 half-lives to reach steady-state, drug washout should be completed by 6 weeks. Studies in the 1940s of young women showed that a thiamine-deficient diet caused symptoms of deficiency in about 2–3 weeks [25, 26]. Our study will not restrict thiamine intake through regular diet, so there is no concern of overt symptomatic thiamine deficiency. In HF, there has been one crossover study with thiamine, and a 6-week washout period was used [27].

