### Outcomes

As this is a feasibility study, the primary outcome is recruitment rate with a target to recruit 24 subjects in 11 months for study completion in 18 months. The secondary outcomes will include the following feasibility and clinical outcomes. Feasibility outcomes include refusal rate (number of eligible patients who refuse to participate), retention rate (number of enrolled patients completing the study), and compliance rate (measured by proportion of participants taking at least 80% of their study medications).

Secondary clinical outcomes include LVEF and peak global longitudinal strain (GLS, %), NT-proBNP, NYHA functional class, quality of life score, and clinical events, which will all be measured at 0, 3, 4.5, and 7.5 months. GLS and LVEF will be measured on 2D/3D transthoracic echocardiography. The change in GLS and LVEF with supplementation will be used to detect improvement in cardiac function. Change in NT-proBNP reflects HF severity and prognosis [28]. The change in NYHA functional class will be used to track changes in HF symptoms. For quality of life changes, we selected the Kansas City Cardiomyopathy Questionnaire (KCCQ), which is a self-administered disease-specific questionnaire [29]. It has been shown to be responsive to change in large HF trials [30]. For clinical events, all-cause mortality, HF hospitalizations (hospital stay of ≥ 24 h with confirmed diagnosis of HF using the Boston HF criteria), and HF emergency room (ER) visits (hospital stay < 24 h) will be recorded.

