### Participant timeline

After randomization, patients will attend four study visits: at 0, 3, 4.5, and 7.5 months (Fig. 1). Patients will undergo the following tests at the first visit: (i) 2D/3D transthoracic echocardiogram (determine LVEF and GLS) and (ii) blood sampling for baseline NT-proBNP and erythrocyte TPP (approximately 20 ml of blood). Patients will be instructed not to take any biotin-containing supplements on the day of bloodwork as these can interfere with NT-proBNP assay [33]. Patients will also be asked to complete the KCCQ, followed by an interview with the research nurse for (i) NYHA symptoms, (ii) clinical and medication history, and (iii) physical examination and vital signs. Thereafter, patients will be given a 3-month supply of the study drug to take once a day. Patients will return to the clinic for reassessment and repeat measurements of the above parameters at 3 months. Following a 6-week washout period, patients will attend the 4.5-month visit and the same parameters are measured. The patients will take the alternate drug assignment for another 3 months, followed by a final visit at 7.5 months to measure the parameters. Deaths, hospitalizations, and ER visits will be recorded at each follow-up. The study nurse will look at admission records from local hospitals, including St. Joseph’s Healthcare Hamilton and Hamilton Health Sciences, and ask the patient or caregiver for admissions outside Hamilton. Deaths will be determined from local hospital records or by calling the patient’s emergency contact. If a patient does not attend follow-up visit, contact will be made via phone or caregiver.

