### Sample size and recruitment

Using a 95% confidence interval and assuming that 40% of eligible participants will consent to participate in the study, we will need to approach 78 participants in order to recruit 24 (12 per arm). This recruitment rate is based on previous experience with other clinical trials conducted at our site with a similar population. Twelve participants per arm are sufficiently large to inform the feasibility outcomes of the trial and to provide sufficient precision around effect estimates and their variances [34, 35]. Our feasibility trial will be used to inform the following: (i) sample size and power calculations, (ii) expected event rate, (iii) flow of participants, and (iv) dropout rates. This study aims to inform a definitive RCT with clinical endpoint of composite of all-cause mortality and HF hospitalizations.

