### Statistical analysis

The process of patient selection and flow throughout the study will be summarized using a flow-diagram. Patient demographics and baseline clinical outcome variables will be summarized using descriptive measures. Data will be analyzed based on the intention-to-treat principle, i.e., data for each participant will be analyzed according to allocation irrespective of whether they complied during the treatment period. Missing data will be replaced using multiple imputation techniques [31]. A secondary per-protocol sensitivity analysis will be conducted for comparison. Although our washout period should be sufficient, we will do a pre-test analysis to check for carry-over effects between the groups. The primary feasibility outcome is reached when 24 patients are recruited within 11 months. Other feasibility thresholds are listed in Table 1. Continuous secondary outcome measures will be tested using analysis of covariance (ANCOVA), with outcome measures adjusted for baseline measures and allocation. McNemar’s test will be used for categorical outcomes. The KCCQ will be analyzed descriptively. All tests will be two-sided, meaning that an effect in either direction will be interpreted. The level of significance is set at *α* = 0.05. Baseline characteristics and results will be reported as means (standard deviation), medians (interquartile range), counts (percentages), 95% confidence intervals, and levels of statistical significance where appropriate. Data will be analyzed using SAS 9.4 (SAS Institute, Cary, NC) and reported according to the CONSORT statement [36].

**Table 1 Tab1:** Outcome measures

Outcome measure	Scale	Type	Measure	Method of analysis
Feasibility outcomes				
Enrollment rate per year	Ratio	Continuous	Number of participants enrolled per year	Feasibility threshold: 24 patients per year
Refusal rate	Ratio	Continuous	Number of eligible patients refusing to participate	Feasibility threshold: < 40%
Retention rate	Ratio	Continuous	Number of participants completing study	Feasibility threshold: > 80%
Compliance rate	Ratio	Continuous	Number of participants taking study drug appropriately (≥ 80% study drug)	Feasibility threshold: > 90%
Clinical outcomes				
Imaging changes	Ratio	Continuous	Change in global longitudinal strain on speckle tracking echocardiography and ejection fraction	ANCOVA
Biomarker changes	Ratio	Continuous	Change in NT-proBNP	ANCOVA
Functional changes	Ratio	Categorical	Changes in NYHA class	McNemar’s test

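### The protocol's half-life argument does not show complete washout by six weeks: its own inputs require 36 to 90 days

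*Protocol article*

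**What the plan says.** The Washout period section of the protocol article states that "the half-life of thiamine is 9–18 days based on a physiology study in young healthy men". From this it concludes: "Assuming 4–5 half-lives to reach steady-state, drug washout should be completed by 6 weeks". It offers two further remarks. Older studies in young women found deficiency symptoms after about 2–3 weeks on a thiamine-deficient diet. There is also a precedent: "In HF, there has been one crossover study with thiamine, and a 6-week washout period was used".

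Statistical analysis then relies on the conclusion: "Although our washout period should be sufficient, we will do a pre-test analysis to check for carry-over effects between the groups". Continuous secondary outcomes are to be analysed by ANCOVA, "with outcome measures adjusted for baseline measures and allocation".

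Outcomes lists LVEF, GLS, NT-proBNP, "NYHA functional class, quality of life score, and clinical events, which will all be measured at 0, 3, 4.5, and 7.5 months". Every measure is therefore taken again at the end of washout. Participant timeline uses the word baseline for the first visit: "blood sampling for baseline NT-proBNP and erythrocyte TPP".

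**The concern.** The half-life sentence is a calculation with all its inputs given, and over most of the stated range the result does not follow. The six-week figure agrees with the lower end of the half-life range, and the upper end is left out. Nothing in the article says that only the lower end was meant. This is a misstatement rather than a detail left to an analysis plan, and Statistical analysis repeats it when it calls the washout sufficient.

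The stake is the set of secondary clinical measures taken at month 4.5. In the thiamine-first group, residual drug could still be acting at that visit. If the month-4.5 value is subtracted or adjusted for as the period-2 baseline, part of the thiamine effect enters the placebo period. The feasibility trial is also meant to inform the procedures and sample size of a definitive trial, so the washout rationale should be right before it is reused.

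**Working it through.** **Inputs from the protocol article.** Half-life of 9–18 days and a rule of 4–5 half-lives (Washout period). Washout of 6 weeks = 42 days, and 90 days of treatment per period (Randomization, enrolment, and crossover arrangement). Twelve per arm (Sample size and recruitment). Pooled LVEF effect of 3.28 points (Discussion).

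**1. Reproducing the plan's figure.** At the shortest half-life, 42/9 = 4.67, which lies within 4–5. This is the end of the range at which six weeks agrees with the rule.

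**2. The whole range.** Time needed = k × half-life, with k = 4 or 5. Fraction remaining after 42 days = 2^(−42/half-life), assuming one-compartment first-order elimination.

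| Half-life (days) | 4 half-lives (days) | 5 half-lives (days) | Half-lives in 42 days | Remaining at 42 days |
|---|---|---|---|---|
| 9 | 36 | 45 | 4.67 | 3.9% |
| 10.5 | 42 | 52.5 | 4.00 | 6.3% |
| 13.5 | 54 | 67.5 | 3.11 | 11.6% |
| 18 | 72 | 90 | 2.33 | 19.8% |

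Of the four corners (36, 45, 72 and 90 days), only 36 fits within 42. The 4-half-life rule needs a half-life of at most 42/4 = 10.5 days. The 5-half-life rule needs at most 42/5 = 8.4 days, which is below the stated range. By the plan's own rule, complete means a residual of 2^−4 = 6.3% down to 2^−5 = 3.1%. Counting 1.5 months as 45.7 days still leaves 3.0–17.2%.

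**3. Residual at the end of period 2.** In the thiamine-first group, month 7.5 falls 42 + 90 = 132 days after the last dose. At 18 days, 2^(−132/18) = 0.0062, so at most 0.6% remains.

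**4. Conditional bias.** Suppose the effect E is proportional to the drug present, and month 4.5 is the period-2 baseline. Let r42 and r132 be the fractions remaining at 42 and 132 days. With raw change scores, the thiamine-minus-placebo contrast is E(1 + r42 − r132) in the thiamine-first group and E in the placebo-first group. Averaging the two gives a relative bias of (r42 − r132)/2:

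- 18 days: (0.198 − 0.006)/2 = 0.096, or about 0.3 LVEF points on 3.28
- 13.5 days: (0.116 − 0.001)/2 = 0.057, or 0.19 points
- 9 days: (0.039 − 0.000)/2 = 0.020, or 0.06 points

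Under ANCOVA the residual is multiplied by the covariate slope. At 18 days with assumed slopes of 0.5–0.7 the bias is 4.7–6.6%. With end-of-period values only, it is −r132/2 = −0.3% at 18 days.

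**5. What the planned pre-test can show.** The article does not name the test. Assume a two-sample t-test with 12 per sequence at two-sided 0.05. Then 80% power needs a difference of 1.2 SD. The 18-day residual is 0.198 × 3.28 = 0.65 LVEF points. With an assumed SD of 6–10 points, power to detect it is 5–7%.

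**6. Precision cost of leaving month 4.5 out of the main comparison.** Under equal correlation between visits it is nil. Under serial decay with an assumed 3-month correlation of 0.6, 0.7, 0.8 or 0.9, the standard error is 1.010, 1.018, 1.029 or 1.043 times that of the ANCOVA using month 4.5, so roughly 0–4% wider overall.

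**The case against.** The sentence is hedged and is true at the short end of the range, where 42 days lies within 4–5 half-lives. That stands, but the section quotes the full range and draws one conclusion from it.

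The protocol has other supports. The earlier crossover study is a precedent for the length. The Discussion describes it as 300 mg for 28 days in nine patients, whereas this trial gives 500 mg for 90 days, so it does not show complete washout here. The diet studies may hint at quick functional depletion, but they concern onset of symptoms on a restricted diet, not clearance after supplementation. The pre-test shows that carry-over was considered, but a null result with 12 per sequence would say little.

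The residual percentages are themselves model-based. They apply a tracer half-life from young healthy men to high-dose supplementation in older patients with heart failure, and the Background puts total body stores at only 25–30 mg. This objection stands: 4–20% is what the protocol's own premise implies, not a measured residual.

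A reader might go further and infer that six weeks is too short, or that the treatment comparison is biased. The documents support neither. They contain no clearance data for this population. They do not name month 4.5 as the period-2 baseline, and the one use of baseline in Participant timeline points to month 0. If month 0 is subtracted in both periods, the contrast reduces to month 3 against month 7.5, which is nearly free of residual drug. Not specifying the visit is the kind of detail an analysis plan may settle, and is not counted here as a fault.

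**Conclusion.** The point holds as a minor correction. The claim of completeness by six weeks does not follow from a half-life of 9–18 days and a 4–5 half-life rule. It is met at four half-lives only up to 10.5 days, and the full range calls for 36–90 days. Under first-order elimination at the cited half-life, about 4–20% of the drug could remain at month 4.5.

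The consequence is limited. Recruitment and the other feasibility outcomes do not depend on washout. For the secondary clinical measures, bias requires both a month-4.5 baseline and an effect that tracks drug level. Even then the upper bound is about 10% of the effect, for raw change scores at the longest half-life, and it is smaller under ANCOVA or a shorter half-life. The slopes, SDs and correlations used above are assumptions. The arithmetic on the half-lives is not.

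**What to change.** **Washout period.** Replace the completeness claim with: *Six weeks covers 2.3–4.7 half-lives over the 9–18 day range, so, assuming first-order elimination, about 4–20% of drug may remain; a 6-week washout was also used in one earlier HF crossover study.*

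**Statistical analysis.** Replace the opening clause that calls the washout sufficient with: *Because washout may be incomplete at the upper end of the half-life range,* and keep the planned carry-over check. Make the main thiamine–placebo comparison of LVEF, GLS and NT-proBNP within participants on end-of-period values at months 3 and 7.5. Treat any analysis with a month-4.5 baseline as a sensitivity analysis. Report the month-4.5 erythrocyte TPP by sequence as the direct washout check.

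**Cost.** No new visits or samples are needed, since all these measures are already scheduled at months 0, 3, 4.5 and 7.5. The protocol would carry a less favourable statement about washout, and the main comparison would have a standard error roughly 0–4% wider under the assumed correlations. A longer washout is not requested; covering the full range would add 30–48 days per participant (72 − 42 to 90 − 42).
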